## Abstract

**Introduction:**

Postnatal vitamin D supplementation may be associated with a reduction in IgE-mediated food allergy, lower respiratory tract infections and improved bone health. Countries in the Northern hemisphere recommend universal infant vitamin D supplementation to optimise early vitamin D levels, despite the absence of large trials proving safety or efficacy for any disease outcome. With the aim of determining the clinical and cost-effectiveness of daily vitamin D supplementation in breastfed infants from age 6–8 weeks to 12 months of age, we have started a double-blind, randomised, placebo-controlled trial of daily 400 IU vitamin D supplementation during the first year of life, VITALITY.

**Methods nd analysis:**

Infants (n=3012) who are fully breastfed and not receiving vitamin D supplementation will be recruited at the time of their first immunisation, from council-led immunisation clinics throughout metropolitan Melbourne, Australia. The primary outcome is challenge-proven food allergy at 12 months of age. Secondary outcomes are food sensitisation (positive skin prick test), number of lower respiratory infections (through hospital linkage), moderately-severe and persistent eczema (by history and examination) and vitamin D deficiency (serum vitamin D <50 nmol/L) at age 12 months. The trial is underway and the first 130 participants have been recruited.

**Ethics and dissemination:**

The VITALITY study is approved by the Royal Children's Hospital (RCH) Human Research Ethics Committee (#34168). Outcomes will be disseminated through publication and will be presented at scientific conferences.

**Trial registration numbers:**

ANZCTR12614000334606 and NCT02112734; pre-results.

Strengths and limitations of this study
Allergic disease is on the rise.Vitamin D deficiency has been associated with the development of food allergy in infants.Vitamin D status appears to play an important role in the adequacy of immune responses to viral respiratory tract infections.Large scale trials of postnatal vitamin D for any disease outcome are lacking.Vitamin D supplementation could optimise infant immune health in the first year of life reducing the risk of allergic disease and respiratory diseases.

## Introduction

Vitamin D is likely to play a role in early infant immune health, with emerging evidence that early life vitamin D deficiency increases the risk of developing childhood diseases such as food allergy^1^ lower respiratory infections (LRIs)^2^ and eczema.^3^ A marked shift to vitamin D deficiency in early life in modern populations may be an underlying driver of the reported rise in allergic diseases including food allergy and eczema.

The rise in food allergy in developed countries is well documented.^1^
^4^
^5^ The increase is most pronounced in children under 5 years of age which suggests a causal role for early life determinants. Recent evidence suggests that low vitamin D at birth or during infancy is associated with an increased risk of food allergy^6^ and eczema.^7^ In addition food allergy and eczema prevalence is higher the further from the equator a person resides, lending support to the hypotheses that low vitamin D (through low ultraviolet (UV) exposure) may play a role in aberrant immune development in early life and increase the risk of developing food allergy and eczema.^3^ Food allergy is one of the earliest manifestations of the immune deviation,^8^ but also strongly coassociates with eczema in infancy and asthma later in life.^9^

Vitamin D supplementation in the first year of life has also been associated with a reduced risk of LRIs^10^ and reduced recovery time in infants with acute bronchiolitis.^11^ Since early life wheezy LRIs are also strongly associated with longer term respiratory outcomes including asthma^12^ understanding the role of vitamin D in the risk of early life respiratory diseases is also important.

Vitamin D deficiency (currently defined as 25OHD3<50 nmol/L) has become more common in modern communities over time, presumably due to inadequate sun exposure resulting from indoor activities and skin cancer concerns.^13^ Vitamin D deficiency is common in Victoria, Australia and also appears to be increasing among pregnant women^14^ and infants.^6^ In addition, the prevalence of infant vitamin D deficiency was fourfold higher among fully breastfed infants than fully formula fed (p<0.001) even at 12 months after solid food had been introduced.^15^

Unlike other countries in the Northern Hemisphere, Australia does not recommend universal vitamin D supplementation. Furthermore as one of the few countries that does not routinely fortify the food chain supply, Australia is uniquely placed internationally to assess the role of vitamin D in early life development.

## Objectives

With the ultimate goal of developing improved public health guidelines for vitamin D supplementation of infants, we aim to determine if vitamin D supplementation in infants from 6 to 8 weeks of age leads to a reduction in the following during the first year of life:
Challenge-proven food allergyLower respiratory infectionsFood sensitisationDoctor diagnosed eczemaVitamin D deficiency

## Methods and analysis

### Design

VITALITY is a double-blind, randomised, placebo-controlled trial of vitamin D supplementation during the first year of life. The trial will be conducted and reported according to CONSORT^16^ guidelines with the cost-effectiveness analysis conducted and reported according to CHEERS guidelines.^17^

### Setting and participants

The trial will be conducted in 6–8 week old breast fed infants not already receiving vitamin D supplementation. Infants will be recruited from council run immunisation sessions within Melbourne, Australia. The study diagram is shown in figure 1. We aim to recruit 1506 infants per arm, 3012 total (see sample size). The study is restricted to breast fed infants because formula feeding from birth can be equivalent to vitamin D supplementation as formula contains approximately 400 IU of vitamin D/L. The amount of formula that infants consume by age 6 months is based on body weight and amount of solid food consumed but generally can considered to be equivalent to the infant receiving <400 IU.

**Figure 1: BMJOPEN2015009377F1:**
[figure not shown]
Study diagram.

### Inclusion and exclusion criteria

*Inclusion criteria*: Healthy, term, breastfeeding 6–8 week old infants. Infants of mothers who intend to continue predominantly breastfeeding until 6 months will be recruited since formula feeding is a surrogate form of partial vitamin D supplementation.

*Exclusion criteria*: Infants with the following will be excluded: already receiving vitamin D supplementation, born premature (<37 weeks)/low birth weight (<2500 g), multiple births, poor health due to a current or past significant disease state or congenital abnormality or infants on medication that interfere with vitamin D metabolism. Mothers who receive antenatal vitamin D supplementation will not be excluded because in our setting, this has not been shown to be protective against postnatal infant vitamin D deficiency.^15^

### Randomisation

Randomisation will be undertaken using a web-based randomisation system set up within the trial database (REDCap). The randomisation schedule will be generated using permuted blocks of variable lengths by an independent statistician. To ensure concealment of allocation participants will only be randomised once they clearly meet inclusion criteria. Participants, their parents and all members of the study team, aside from the clinical trials pharmacist, will remain blinded to treatment allocation throughout the trial.

### Intervention

Infants will be randomly assigned to receive 400 IU vitamin D3-Cholecalciferol (1 drop, 0.03 mL) (Baby D drops) or an identical placebo (1 drop vegetable oil) daily until 12 months of age. Both active and placebo interventions will be supplied by the D Drops Company, Ontario, Canada which currently provides the active product commercially under the regulation of Health Canada's Natural Health Product Directorate.

The current daily dose recommended for infants in the first year of life is 400 IU in all available published international guidelines; USA^18^ and UK National Health Service (NHS) guidelines. A daily dose of 400 IU administered from around 4 weeks of age was sufficient to increase vitamin D levels to ≥50 nmol/L in 98% of infants by 3 months of age.^19^

### Compliance

We have developed an iPhone application to remind study participants to give their infant the study medication and to monitor dosing compliance. This information can be emailed from the app to [contact] and incorporated into the REDCapdatabase. An android-based application is in development. For participants without smart phones, a paper diary system is available. These can be sent back via mail or photographed and emailed. Participants are asked to send their empty bottles of study medication to the Clinical Trials Pharmacy for re-weighing to measure compliance with daily dosing. To date compliance with daily dosing is 90% based on the number of returned, completed diaries.

### Outcomes

*Primary*
Challenge-proven food allergy at 12 months of age.

*Secondary*
Number of LRIs by 12 months of age;Food sensitisation (positive skin prick test) at 12 months of age;Moderately-severe and persistent eczema at 12 months of age;Vitamin D deficiency at 12 months of age.

### Ethics and dissemination

The study has been approved by the Royal Children's Hospital (RCH) Human Research Ethics Committee (#34168) and is registered with the Australia & New Zealand Clinical Trials Registry (ANZCTR12614000334606) and U.S. National Institutes of Health (NCT02112734). Written informed consent will be obtained from all participants included in the trial. Participants will be informed that they are not obliged to take part in the study and are free to withdraw at any time without negative consequences on their future care. The privacy of participants will be protected and their names and personal information will be kept confidential. No serious adverse reactions are anticipated in the trial but these will be monitored by the Data Safety and Monitoring Committee. Outcomes will be disseminated through publication according to the SPIRIT statement and will be presented at scientific conferences.

### Data collection

Table 1 summarises timing of measures, described in more detail below. Web-based questionnaires will be administered to parents at baseline and when their infant is aged 3, 6, 9 and 12 months. Infants will be invited in for a clinical assessment, blood sample and allergy testing at age 12 months at the completion of the intervention. An optional RCH clinic visit at age 6 months will be offered to participants and will include an eczema examination and blood draw. Daily diaries will be used to record compliance with drug dosing, changes to infant feeding, new allergy symptoms, medication use and medical visits to inform the economic evaluation.

**Table 1 BMJOPEN2015009377TB1:** Summary and timing of measures

[figure not shown]

SCORAD, Scoring of Atopic Dermatitis; SPT, skin prick test.

### Primary outcome

*Challenge confirmed food allergy*: These will be undertaken in all participants with a positive skin prick test to food allergens at age 12 months. Food challenges will follow Australasian Society of Clinical Immunology and Allergy (ASCIA) guidelines as used by the RCH Allergy Clinic and validated within our HealthNuts study in which we undertook more than 1800 oral food challenges^4^
^6^
^20^ at age 12 months.

### Secondary outcomes

*LRIs*: The parent questionnaires will capture information on bronchiolitis, healthcare visits/hospital admissions and medication use in the past 3 months. We will access general practitioner (GP) or hospital records to obtain accurate data on lower respiratory infections.

*Food sensitisation*: Sensitisation to a panel of allergens will be assessed in all participants at 12 months of age: cow's milk, egg, peanut, cashew, sesame. Skin prick allergy testing will be performed according to standard guidelines as per previous HealthNuts protocol.^20^

*Eczema*: Eczema history will be assessed by the U.K. Working Party’s Diagnostic Criteria for Atopic Dermatitis using parent questionnaire data. Severity of eczema will be assessed using Scoring of Atopic Dermatitis (SCORAD)^21^ at baseline/12 months as follows: Mild—SCORAD <25, Moderate—SCORAD, 25–50, Severe—SCORAD ≥50. Persistent eczema will be assessed if age of onset of eczema was by 9 months and evident at age 12 months.

*Vitamin D deficiency*: Infant 25OHD3 levels and metabolites including the C3-epimer of 25OHD3 will be measured using liquid chromatography-tandem mass spectrometry.^22^ The method will be referenced to the Joint Commission for Traceability in Laboratory Medicine's recommended reference standard to provide accuracy for the vitamin D result. Participant's vitamin D status will be defined by their blood 25OHD3 level, as: severely deficient <12.5 nmol/L; moderately deficient 12.5–25 nmol/L; mild deficiency 26–49 nmol/L; sufficient ≥50 nmol/L; and elevated >220 nmol/L.^23^

*Parent Baseline Questionnaire*: To check that potential environmental and other confounding factors are balanced between the two randomisation groups, baseline parent questionnaires will collect data on: parental smoking, medication use, parental ancestry, ethnicity, education, employment, occupation, family history of allergy, use of supplements including vitamin A, D and cod liver oil, number of siblings; and pet ownership.

*Parent Questionnaire (3 monthly)*: To capture dietary vitamin D intake and environmental UV radiation (UVR) exposure, we will ask questions about maternal vitamin D supplements, infant diet, maternal and infant sun exposure and sun protective behaviours as in our previous work,^15^ for example, number of hours spent in the sun per day, during summer or winter, weekends and holidays, will be collected for mother and child. Cumulative UVR dose will be calculated as the product of time spent outdoors and ambient UVR during the period. Composite skin exposure and sun protection indices will be measured. We have established that composite maternal UVR dose (OR 0.50 (95% CI 0.37 to 0.69) p<0.001) and maternal skin exposure index (OR 0.81 (95% CI 0.66 to 0.98) p=0.03) were associated with breastfed infant vitamin D status but infant time in the sun during the first year was not.^15^ Infant feeding (amount of breastfeeding, formula feeding and type of formula, introduction of solid foods) will also be recorded. At 12 months only, infant skin/hair/eye colour will be assessed using a standardised, validated chart. We have validated that the charts predict (p<0.001) skin melanin density by spectrophotometer.^24^

*Blood samples (12 months)*: Peripheral blood mononuclear cells will be separated from whole blood and stored in liquid nitrogen, and plasma will be stored and frozen in our −80°C freezer. These will be retained for future analysis to evaluate immune function including regulatory T cell and cytokine assays.

*Newborn screening (Guthrie) card*: consent will be obtained at recruitment to access Guthrie cards to undertake assessment of vitamin D levels at birth.

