### Start of the study

The trial started in December 2014, with n=130 participants as of June 2015. Of those eligible 48%% consented to participate. To date 13% have dropped out, on average within the first 6 weeks (5.9±4.0, weeks, mean±SD, min 0.4-max 15.4 weeks) after recruitment (main reasons include: difficult to give daily drops, too busy to comply with the study procedures). There have been no reported adverse events. Approximately half approached have an iPhone and 63% of those have activated use of the VITALITY iPhone drug compliance app. Table 2 shows demographic information for the first 130 participants to be enrolled.

**Table 2 BMJOPEN2015009377TB2:** Baseline demographics for first participants n=130*

Characteristic	
Maternal age mean±SD (minimum–maximum)	33.7±4.6 year (19.4–45.5)
Paternal age mean±SD (minimum–maximum)	36.3±5.5 years (21.0–50.0)
Baby age mean±SD (minimum–maximum)	7.4 weeks±1.2 (6.0–11.5)
Maternal education n (%)	
Year 12	10 (9.0)
Trade certificate	9 (8.3)
University degree	56 (51.8)
Higher degree (eg, PhD, masters)	28 (25.9)
Other	5 (4.6)
Paternal education	
Year 12	14 (13.0)
Trade certificate	25 (23.1)
University degree	45 (41.7)
Higher degree (eg, PhD, masters)	22 (20.4)
Other	2 (1.8)
Marital status	
Single	1 (1.0)
Married	91 (84.3)
Defacto	14 (12.07)
Separated	1 (1.0)
Other	1 (1.0)
Maternal country of birth	
Australia	79 (73.1)
Other country	29 (26.8)
Paternal country of birth	
Australia	70 (65.0)
Other country	38 (35.0)
Family history of asthma	
No	54 (50.0)
Yes	54 (50.0)
Family history of eczema	
No	61 (57.0)
Yes	44 (41.1)
Do not know	2 (1.9)
Family history of food allergy	
No	75 (70.0)
Yes	30 (28.1)
Do not know	2 (1.9)
Maternal smoking	
No	104 (97.2)
Yes	3 (2.8)
Sex of baby	
Female	48 (45.7)
Male	57 (54.3)
Baby country of birth	
Australia	105 (100.0)
Feeding some formula	
No	64 (64.0)
Yes	36 (36.0)
If feeding some formula, infant age when started, weeks	
Mean±SD (minimum–maximum)	2.5±3.1 (0.0–12.0)
If feeding some formula, times given since birth, days	
Mean±SD (minimum–maximum)	16.0±18.3 (1.0–71.0)

Withdrawn from study n=19.

*Complete data set for n=108 mothers and n=105 infants.

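### The LRI count has an end age but no start, so its stated window takes in about 6–8 weeks before randomisation; if infections from that period are counted, the treatment contrast is modestly diluted

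*Protocol article*

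**What the plan says.** All statements in the protocol article about the LRI window are in terms of the infant's age.

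- **Outcomes:** the secondary outcome is "Number of LRIs by 12 months of age". It has an end and no beginning.
- **Objectives:** the aim is to learn whether "vitamin D supplementation in infants from 6 to 8 weeks of age leads to a reduction in the following during the first year of life".
- **Data collection:** "Web-based questionnaires will be administered to parents at baseline and when their infant is aged 3, 6, 9 and 12 months".
- **Secondary outcomes, LRIs:** "The parent questionnaires will capture information on bronchiolitis, healthcare visits/hospital admissions and medication use in the past 3 months". The next sentence adds a second source: "We will access general practitioner (GP) or hospital records to obtain accurate data on lower respiratory infections". The Abstract names hospital linkage. No start date is attached to either record source.
- **Setting and participants:** "The trial will be conducted in 6–8 week old breast fed infants not already receiving vitamin D supplementation". Table 2, under Start of the study, gives the age of the first infants as mean 7.4 weeks, SD 1.2, range 6.0 to 11.5.

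The paragraph on the baseline questionnaire (Secondary outcomes) lists its topics, such as smoking, medication use, family history, supplements, siblings and pets. Earlier respiratory infection is not among them.

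**The concern.** Taken together, the four follow-up questionnaires at 3, 6, 9 and 12 months, each looking back 3 months, cover the whole of the first year from birth. Treatment can only act after randomisation. An infant who had bronchiolitis at 5 weeks and has recovered is not clearly shut out by the exclusion criteria. That infant could enter the trial already carrying an LRI that neither the active drops nor the placebo could have influenced.

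Such events fall equally on both arms in expectation. They add the same amount to each arm's count, so the ratio between arms moves towards 1 and power falls. LRI reduction is a named objective, and the Discussion claims adequate power for disease outcomes that include LRIs, so avoidable dilution deserves a correction.

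**Working it through.** **The plan's own figures.** The article gives no LRI rate, target effect or power, so there is no LRI figure to reproduce. The stated sample size concerns food allergy: 1205 per group, 2410 in total, and 2410/0.80 = 3012.5 against the stated 3012. That is consistent and not affected by this point.

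**Inputs from the article.** Age at randomisation 6 to 8 weeks as planned, mean 7.4 weeks observed; recall 3 months; 1205 analysed per arm; two-sided 5% test.

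**Conversions.** One year = 52.18 weeks; 3 months = about 13.04 weeks.

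**Step 1: share of time before randomisation.**

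| Age at randomisation | Share of first year | Share of the age-3-month look-back |
|---|---|---|
| 6 weeks | 6/52.18 = 11.5% | 6/13.04 = 46% |
| 7.4 weeks | 7.4/52.18 = 14.2% | 7.4/13.04 = 57% |
| 8 weeks | 8/52.18 = 15.3% | 8/13.04 = 61% |

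**Step 2: dilution of the rate ratio.** Let f be the share of the control arm's expected LRIs that precede randomisation. If those events are counted, apparent RR = RR × (1 − f) + f.

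With a constant LRI rate over the year (assumption), f equals the share of time. At 7.4 weeks:

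- RR 0.70: 0.70 × 0.858 + 0.142 = 0.743
- RR 0.80: 0.80 × 0.858 + 0.142 = 0.828

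At 6 and 8 weeks, 0.70 appears as 0.734 and 0.746.

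**Step 3: relax the constant rate.** Let the rate before randomisation be k times the later rate (assumption). Then f = 7.4k / (7.4k + 44.78), where 44.78 = 52.18 − 7.4.

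| k | f | RR 0.70 appears as |
|---|---|---|
| 0.25 | 4.0% | 0.71 |
| 0.5 | 7.6% | 0.72 |
| 1 | 14.2% | 0.74 |
| 1.5 | 19.9% | 0.76 |

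**Step 4: power, as illustration only.** Wald test on the log rate ratio with expected counts per infant m₀ and m₁ and dispersion d: power = Φ( |log(m₁/m₀)| / √[(1/m₀ + 1/m₁ + 2d)/1205] − 1.96 ). Counting from randomisation uses m₀ = 0.858λ and m₁ = RR × 0.858λ. Counting from birth uses m₀ = λ and m₁ = λ(0.858 RR + 0.142). The yearly rate λ, the dispersion, the true ratio and the constant rate are all assumptions.

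| λ per infant-year | d | True RR | From randomisation | From birth |
|---|---|---|---|---|
| 0.1 | 0 | 0.70 | 64% | 57% |
| 0.2 | 0 | 0.70 | 91% | 86% |
| 0.3 | 0 | 0.70 | 98% | 96% |
| 0.2 | 0.5 | 0.80 | 54% | 47% |
| 0.4 | 0.5 | 0.80 | 80% | 73% |
| 0.6 | 0.5 | 0.80 | 92% | 86% |

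In these scenarios the loss runs from about 2 to 8 percentage points.

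**The case against.** A reader might infer that infections before randomisation will be counted as outcome events. The article does not say so. A recall period describes what is captured, not which episodes enter the analysis. Hospital and GP records would normally carry dates, so early episodes could be removed without any change of design. The daily diaries, which record dosing and medical visits, accompany treatment and so cover time after randomisation. The full protocol or analysis plan, not shown here, may set a start date, and the actual questionnaire wording cannot be seen. All of this stands, and it limits the point to what follows if the stated window is applied literally.

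It does not remove the point. The article does more than leave out a detail: it gives an age-based outcome window, an age-based questionnaire schedule and a recall length that together reach back to birth. Dated records make the correct rule possible but do not state it. The listed baseline topics contain nothing that would separate earlier infections.

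The objection that the size is uncertain is also fair. The 14% is a share of time and becomes a share of events only under a constant rate. Enrolling healthy term infants may remove some with serious early illness and lower the share. That is why the range over k is shown.

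**Conclusion.** The point holds in conditional form. The stated LRI window includes roughly 6–8 weeks before randomisation, and nothing in the article excludes infections in that period. If they are counted, a true rate ratio of 0.70 appears as about 0.74 under a constant rate, and as 0.71–0.76 if the early rate is 0.25 to 1.5 times the later rate. The power losses rest further on assumed LRI rates and dispersion.

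The consequence is modest attenuation of one secondary outcome. Because the early events are balanced in expectation by randomisation, they create no false-positive bias. The primary outcome and sample size are untouched. A reader might also infer that the economic evaluation is distorted. The documents do not support that for its headline result, which is cost per case of food allergy averted; LRI costs are collected, but modelling of secondary outcomes is only a possible extension.

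**What to change.** 1. Define the outcome as the number of LRIs with onset from randomisation to 12 months of age.
2. Word the recall period of the age-3-month questionnaire as the time since joining the study.
3. Count record-confirmed LRIs only if dated after randomisation.
4. Ask about earlier LRIs in the baseline questionnaire and report them as a baseline characteristic.

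The cost is one sentence in the outcome definition, a wording change in one questionnaire and one added baseline item. Slightly fewer events are counted, but the events lost carry no information on treatment effect. When the article was written, 130 of the planned 3012 infants had been enrolled, so the wording could be settled before most data were collected. For infants already enrolled, dated records allow the same start to be applied.
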